**Figure 4 figure4:**
[figure not shown]
Diagram representing the interrupted times series design.

### What Are the Planned Trial Interventions?

#### Experimental Group

Participants from trauma centers assigned to the experimental group will receive a password to access and complete the Wiki101 course and to use WikiTrauma. They will receive three reminders at 2-week intervals to complete Wiki101. Before and after each Wiki101 course, participants will be administered a validated questionnaire to measure changes in opinion and beliefs about using WikiTrauma. Questionnaires will also be repeated after the prospective 12-month period. After each course, participants will also receive a 2-week reminder about skills taught during the course.

#### Control Group

Participants in the control group will receive an email promoting access to the regular INESSS webpage and will also receive three reminders at 2-week intervals to access the website. They will not have access to view or edit WikiTrauma.

#### Management of WikiTrauma During the Trial

For the purpose of this trial, to monitor its use, and ensure its quality, access to WikiTrauma will be protected by password.

#### Quality of Information Monitoring

Since the wiki content can be constantly changed by the participants, the quality of information and the strength of evidence will be assessed weekly by a medical expert (JL) and monthly by the steering committee using a standardized evaluation form. This committee will edit any serious deviations from recognized standards of care and will flag controversial topics to stimulate discussion within the wiki community.

### What Are the Proposed Practical Arrangements for Allocating Participants to Trial Groups?

All professionals and decision makers working in the four participating trauma centers will be eligible to participate. With the help of the local leaders on the trauma committee, we will recruit as many clinicians (eg, physicians, nurses, respiratory therapists, and pharmacists) and decision makers (eg, heads of Emergency Department, Surgery Department, and Critical Care Department) as possible. All participating trauma committees will also be asked to designate five patient representatives to take part in the construction of various tools designed for their use (eg, decision aids and patient handouts). In each center, we will present the project to the local representatives of each trauma committee. We will provide a hands-on Wiki101 session to all the members of the local trauma committee and the five patient representatives, who will then become the local leaders able to teach their colleagues how to access the wiki and contribute to its content. An online version of Wiki101 will be available to all clinicians and patient representatives for future consultation.

### What Are the Proposed Methods for Protecting Against Sources of Bias?

Although blinding of the participants and randomization are not feasible in this small trial, we will mobilize all efforts to minimize any other sources of bias. All data collectors (medical archivists) will be blinded to the allocation group. Throughout our study, we will prevent contamination by protecting Wiki101 and WikiTrauma by password and note any potential competing intervention. We will also identify any professional working in more than one participating trauma center to consider the impact of this potential source of bias. Wiki101 will be a standardized online training program. We will encourage all participants to complete all 12 months of the study. To minimize a potential Hawthorne effect, our control group will receive an invitation to consult the INESSS website at the beginning of the study. Moreover, our proposed study design of an interrupted time series provides the advantage of controlling for secular trends in the data.

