### What Is the Proposed Trial Design?

This study will be an interrupted time series with a parallel, theory-based process evaluation alongside the trial (see Figure 4). In the context of quality improvement, the interrupted time series is a simple but powerful tool used for evaluating the impact of a quality improvement program [119]. Our time series—repeated observations of the quality of care collected over time—will be divided into two segments. The first segment will comprise 10 retrospective, quarterly measurements of the quality of care measured before our intervention (a period of 30 months), and the second segment will be four prospective, quarterly quality of care measurements after our intervention (12 months). There are 57 adult-designated trauma centers of varying levels in Quebec—three level I, 26 level II, and 28 level III trauma centers. Four trauma centers will be selected in Université Laval's trauma network. We already identified one level I trauma center and a level II trauma center as participants. We will recruit two level III centers to complete our targeted sample of participating centers. Participants will not be blinded to their study assignment, however, all analyses will be blinded. The control group will comprise all of the 53 remaining adult trauma centers in the province.

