### What Are the Planned Inclusion/Exclusion Criteria?

#### Inclusion Criteria

We will select four trauma centers—one level I, one level II, and two level III trauma centers. The two level III centers will be identified by the authors based on their willingness to participate and collaborate with the other trauma centers for the 12-month project. At the individual level, study participants must be decision makers (eg, trauma program coordinators) or health care professionals (eg, emergency physicians, critical care physicians, trauma surgeons, nurses, respiratory therapists, physiotherapists, or pharmacists). Patient representatives will be selected without any restrictions or limitations with regard to their qualifications. These patient representatives could also be caregivers to existing trauma patients. Health care professional students and trainees (eg, residents, medical students, and nursing students) will have the same access to WikiTrauma and Wiki101 as fully certified professionals.

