### Data Analysis

Segmented regression will be used to measure, statistically, the changes in level and slope in the postintervention period compared to the preintervention period [119]. Thus, we will present a regression model with different intercept and slope coefficients for the pre- and postintervention time periods. We will compare the changes in quality of care measured at our four intervention trauma centers to the changes in quality of care measured at the other 53 trauma centers where no experimental intervention occurred. During the implementation period of WikiTrauma, we will continue to measure the impact on the quality of care. However, we will only proceed to compare the change in slope in the postintervention period once WikiTrauma has been fully implemented. We will use a Durbin-Watson test to verify the presence of autocorrelation and use an autoregressive error model to correct for this serial correlation.

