### Ethical Considerations

We will apply for ethical approval to conduct this trial in all four participating trauma centers. All participants will be asked to consent before accessing the wiki for the first time and before any questionnaire administration. Local trauma committees will be consulted and we will obtain approval and support from each trauma center's chief executive officer. Patient participants will also be asked to complete a consent form before participating in any phase of this trial.

A legal disclaimer will also be posted on the wiki site asking participants to always use their clinical judgement first. Clinical judgement should never be replaced by any information found in a protocol based in WikiTrauma. In addition, clinicians should only use the wiki pages that have been approved by their local trauma committee.

All personal information on study participants will remain anonymous and we will not publish the names of any of the participating trauma centers. All sensitive information will be kept in a locked filing cabinet at the principal investigator’s (PI) research center or in a password-protected computer at the research center.

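### The check for staff shared between centers covers only the four intervention sites and leaves out staff shared with the 53 control centers

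*Protocol article*

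**What the plan says.** The section on protecting against bias gives two safeguards that bear on this point. The first is access control: "we will prevent contamination by protecting Wiki101 and WikiTrauma by password". The second is a check on shared staff: "We will also identify any professional working in more than one participating trauma center to consider the impact of this potential source of bias".

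The article is consistent about which centers it calls participating:
- The section on allocating participants: "All professionals and decision makers working in the four participating trauma centers will be eligible to participate".
- The trial design section: "We will recruit two level III centers to complete our targeted sample of participating centers".
- Ethical Considerations: "We will apply for ethical approval to conduct this trial in all four participating trauma centers".

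The comparison group is defined separately: "The control group will comprise all of the 53 remaining adult trauma centers in the province". Data Analysis sets changes at the four sites against "changes in quality of care measured at the other 53 trauma centers where no experimental intervention occurred".

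Three further provisions matter. Under Inclusion Criteria, students and trainees "will have the same access to WikiTrauma and Wiki101 as fully certified professionals". The Control Group section denies controls any access to WikiTrauma. Safety Monitoring and Quality Assurance limits an approved page to the center whose trauma committee approved it, and Ethical Considerations tells clinicians to rely only on locally approved pages.

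**The concern.** Someone who works at two of the four intervention sites is exposed at both by design and takes nothing into the control group. The comparison with controls is at risk when a person who has had the training and holds a password also works or trains at one of the 53 control centers. The shared-staff check is the only stated step that looks for people working at several centers, and read literally it does not look there.

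The route is plausible on the document's own facts. All four sites lie in one university trauma network, trainees have full access, and trained committee members are expected to teach their colleagues. How many people move between intervention and control centers is not stated.

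The analysis describes the 53 centers as places where no experimental intervention took place. If that is not fully true, the comparison is drawn toward no effect. The Sample Size section already concedes that four post-intervention points reduce power. Without a record of the overlap, a null comparison would be harder to interpret.

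**Working it through.** The protocol gives no figure for contamination, so there is none to reproduce. The check is a reading of the text, a count of center pairs, and an illustration of size.

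**1. Center counts (trial design section).** Level I, II and III centers: 3 + 26 + 28 = 57. Controls: 57 − 4 = 53. Both agree with the text.

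**2. Which centers are participating.** The allocation and ethics sections each attach the number four to the term, and the design section applies it to the targeted sample that two level III sites will complete. The pilot-testing section uses the opposite term for sites outside the trial sites. The 53 controls are never called participating centers.

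**3. What the check covers.**
- Intervention–intervention pairs: 4 × 3 / 2 = 6. All are covered, and none carries exposure into the control group.
- Intervention–control pairs: 4 × 53 = 212. None is covered, and these are the pairs that could contaminate the comparison.

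The pair counts show the scope of the rule. They do not say how much overlap exists.

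**4. What the other safeguards cover.**

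| Safeguard | Limits access or use at controls | Records who works at both | Stops carry-over of training |
|---|---|---|---|
| Password | Yes, for people without an account | No | No |
| No WikiTrauma access for controls | Yes | No | No |
| Pages only for the approving center | Yes, as an instruction | No | No |
| Shared-staff check as worded | No | Only among the four sites | No |

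**5. Size under assumed uptake.** Suppose a share c of the intervention effect reaches the control average. With controls weighted equally (an assumption), observed contrast = (1 − c) × true effect.
- c = 0.02 leaves 0.98 of the effect.
- c = 0.05 leaves 0.95.
- c = 0.10 leaves 0.90.
- If 5 of 53 controls take up half the effect, c = (5/53) × 0.5 = 0.047, a shrinkage of 4.7%.

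None of these uptake values comes from the documents.

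**6. What is not affected.** The segmented regression also estimates changes in level and slope within the four sites. Exposure at controls does not enter those estimates.

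**The case against.** The strongest reply is that the tools are restricted by place as well as by account. An approved page is meant only for the center that approved it, clinicians are told to keep to locally approved pages, and nothing provides for control-center committees to approve any. Using a WikiTrauma page at a control center would therefore breach a stated rule. This stands, and it makes large contamination less likely. But it is an instruction on use. It creates no record of who works where, and it does not keep trained staff from applying what they learned.

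A second reply is that the sentence speaks of a source of bias, not of contamination, and may be aimed at dependence between intervention sites, which is worth noting with only four. Or it may be loose wording meant to include controls, since the Control Group section speaks of participants there. On the first reading the check is valid but too narrow; on the second the wording needs correcting. Either way the same change is needed.

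A third reply is that a registration question and a sensitivity analysis are detail for a fuller document. That is fair for their specification. The scope of the check, however, is stated here and leaves out the overlap that matters for the comparison.

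Two stronger readings are tempting, and the documents support neither. A reader might calculate that if one of the two remaining level I controls (3 − 1 = 2) took up half the effect, a level I contrast would shrink by 1/2 × 0.5 = 25%. The arithmetic is right, but the article plans no contrast by level. A reader might also infer that the overlap could never be established later. Users receive a password, consent before first access and complete a questionnaire after 12 months, so they are identifiable and could still be asked.

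**Conclusion.** The point holds, with limited consequence. As worded, the check leaves out people with WikiTrauma access who also work or train at control centers, and no other stated safeguard records them. Any resulting bias affects only the 4-versus-53 comparison and runs toward no effect. It is probably small because it is spread over 53 centers: 4.7% under the assumed uptake above, and 2% to 10% for an assumed c of 0.02 to 0.10. The conclusion rests on reading *participating* as the four intervention sites, which the article's usage supports. That such overlap occurs at all is inferred from the shared network and trainee access. The documents do not show that contamination is present or that the design is invalid.

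**What to change.** Reword the check to cover any professional or trainee with WikiTrauma access who also works or trains in any of the 53 control centers. Overlap among the four sites can still be noted as a matter of dependence between them. Ask for the person's other centers when the password is issued, or at the latest in the 12-month questionnaire. Asking at issue is preferable because it does not depend on recall or on who completes the final questionnaire. Flag the control centers so linked, and report the 4-versus-53 comparison with all controls and again without the linked ones, as a sensitivity analysis.

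The cost is one extra question and one extra analysis, with slightly fewer controls in the latter. The primary comparison and the within-site analysis stay as planned.

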### What Are the Planned Inclusion/Exclusion Criteria?

#### Inclusion Criteria

We will select four trauma centers—one level I, one level II, and two level III trauma centers. The two level III centers will be identified by the authors based on their willingness to participate and collaborate with the other trauma centers for the 12-month project. At the individual level, study participants must be decision makers (eg, trauma program coordinators) or health care professionals (eg, emergency physicians, critical care physicians, trauma surgeons, nurses, respiratory therapists, physiotherapists, or pharmacists). Patient representatives will be selected without any restrictions or limitations with regard to their qualifications. These patient representatives could also be caregivers to existing trauma patients. Health care professional students and trainees (eg, residents, medical students, and nursing students) will have the same access to WikiTrauma and Wiki101 as fully certified professionals.

#### Exclusion Criteria

At the cluster level, a trauma center will not be eligible to participate if more than 50% of the members of the local trauma committee refuse to participate. Reasons for exclusion or refusal to participate will be documented. Pediatric trauma centers will be excluded.

### What Is the Proposed Duration of the Treatment Period?

Wiki101 will take 3 hours to complete for each participant and they will have access to use Wiki101 and WikiTrauma for 12 months.

### What Is the Proposed Frequency and Duration of Follow-Up?

Aside from our pre- and post-Wiki101 questionnaire and the 2-week reminder after completing Wiki101, we will only administer a final questionnaire after the 12-month treatment period.

### What Are the Proposed Primary and Secondary Outcome Measures?

The primary outcome measure will be the change over time in a validated, composite performance indicator score based on 15 process performance indicators found in the Quebec Trauma Registry [4]. The secondary outcome measures will be rates of complications, length of stay, mortality, and the FIM. These will also be found in the Quebec Trauma Registry. Other secondary outcome measures will be the following: (1) intention to use WikiTrauma and the sociocognitive determinants of this intention, (2) the self-reported use of WikiTrauma in clinical practice, (3) the actual frequency of WikiTrauma use—number of visits, length of visits, number of visitors, and number of unique visitors, (4) the quality of information contained within WikiTrauma, (5) the frequency of content modifications—number of visitors having modified content, number of pages modified, number of new pages created, and number of pages having generated an edit war, (6) participants’ comments about what worked and improvements suggested, (7) the estimated annual cost of maintaining WikiTrauma, (8) the cost of delivering Wiki101, (9) the estimated cost of creating new knowledge-decision tools, and (10) the estimated cost of updating old knowledge-decision tools.

### How Will the Outcome Measures Be Measured at Follow-Up?

We will measure quarterly composite performance scores from the Quebec Trauma Registry for all 57 adult trauma centers. Data in the Quebec Trauma Registry is routinely collected in all Quebec trauma centers every 3 months. The composite performance score is calculated as the average of 15 other indicators routinely collected in the Quebec Trauma Registry [4]. This score has good discrimination, construct validity, criterion predictive validity, and forecasting properties [120]. Mortality rates, complication rates (for delirium, pneumonia, and deep venous thrombosis), length of stay, and FIM will also be measured on a quarterly basis for all 57 trauma centers from routinely collected data in the Quebec Trauma Registry. The intention to use WikiTrauma will be measured by a validated questionnaire [40]. The actual wiki use and the frequency of content modification will be measured on a quarterly basis using a Google Analytics account linked to WikiTrauma.

### Safety Monitoring and Quality Assurance

Since participants can change wiki content, the quality of information and the strength of evidence will be assessed weekly by an INESSS medical expert, and monthly by the scientific committee using a standardized evaluation form. This committee will edit any serious deviations from recognized standards of care and will flag controversial topics to stimulate discussion within the wiki community. The quality of different KT tools will be evaluated using the Grading of Recommendations, Assessment, Development and Evaluation (GRADE) methodology for grading quality of evidence and strength of recommendations [121]. To estimate the amount of supervision that was needed by the medical supervisor at INESSS, we will document the number of pages modified and created, and the number of edit wars. In order to ensure that only high-quality and officially approved knowledge tools will be used in clinical practice, wiki pages that are not approved for clinical use by local trauma committees will be color-coded in RED with a warning message to say that the page is currently under construction. Pages that are approved by local trauma committees will be color-coded in GREEN for use only in the trauma center that approved the page. To estimate activity that was generated by our wiki and the amount of supervision that was needed during this trial by the medical supervisor at INESSS, we will study the wiki’s revision history page to document the number of visitors having modified the content, the number of pages modified, the number of new pages created, and the number of pages having generated an edit war [122] on a quarterly basis. An edit war will be defined as more than three reverts by a single editor on a single page within a 24-hour period. An edit that undoes other editors' actions will count as a revert. All cases of potential patient harm reported by any quality assurance committee or participant will be described and declared.

### Sample Size

As a rule of thumb for an interrupted time series, 10 measurement points before and 10 measurements after an intervention provides 80% power to detect a change in level of 5 standard deviations (of the predata) only if the autocorrelation is greater than .4 (ie, extent to which data collected close together in time are correlated with each other) [123]. In our case, we will be able to measure 10 measurement points before (30 months), but the period of observation after our intervention will be limited to 12 months—4 quarters is equal to 4 measurement points. This will decrease our power, but we are currently applying for funding from other sources to collect data for a total of 32 postintervention months (10 quarters).

### Data Analysis

Segmented regression will be used to measure, statistically, the changes in level and slope in the postintervention period compared to the preintervention period [119]. Thus, we will present a regression model with different intercept and slope coefficients for the pre- and postintervention time periods. We will compare the changes in quality of care measured at our four intervention trauma centers to the changes in quality of care measured at the other 53 trauma centers where no experimental intervention occurred. During the implementation period of WikiTrauma, we will continue to measure the impact on the quality of care. However, we will only proceed to compare the change in slope in the postintervention period once WikiTrauma has been fully implemented. We will use a Durbin-Watson test to verify the presence of autocorrelation and use an autoregressive error model to correct for this serial correlation.

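### On one 14-point quarterly series, Durbin-Watson followed by an autoregressive correction does not reliably remove serial correlation; primary inference should rest on center-level changes across all 57 centers

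*Protocol article*

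**What the plan says.** Under What Is the Proposed Trial Design?, the protocol article fixes the length of the series: "The first segment will comprise 10 retrospective, quarterly measurements of the quality of care measured before our intervention (a period of 30 months"). For the follow-up it plans that "the second segment will be four prospective, quarterly quality of care measurements after our intervention (12 months"). That makes 14 quarterly points.

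Data Analysis fixes the model: "Segmented regression will be used to measure, statistically, the changes in level and slope in the postintervention period compared to the preintervention period". It adds that "we will present a regression model with different intercept and slope coefficients for the pre- and postintervention time periods". Serial correlation is handled by one rule: "We will use a Durbin-Watson test to verify the presence of autocorrelation and use an autoregressive error model to correct for this serial correlation".

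The same section announces a comparison of the change at the four intervention centers with the change at the other 53. It does not say whether the autoregressive model is fitted to a pooled series, a difference series or 57 center series, nor what supplies the standard error of the comparison. The section on measuring outcomes at follow-up states that the composite score is obtained each quarter for all 57 adult centers. No autocorrelation is estimated for this score. The only value named, in Sample Size ("only if the autocorrelation is greater than .4"), belongs to a cited power rule.

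**The concern.** Separate intercepts and slopes use four coefficients on 14 points. A fit that flexible absorbs much of the slow drift that positive autocorrelation produces. The residuals then look nearly uncorrelated, Durbin-Watson seldom rejects, and when it does the correction uses an autocorrelation that is too small.

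A second source of error is separate from the first. Only four centers are treated. If centers differ in how their scores change over time, that variation belongs in the uncertainty of a 4-versus-53 comparison, and a correction for serial correlation does not put it there.

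At stake are the p-value and interval for the primary outcome: ordinary drift could be reported as an effect of the intervention.

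**Working it through.** **Inputs.** From the protocol: 10 + 4 quarters; intercept, slope, level change and slope change; Durbin-Watson, then an autoregressive error model; 57 centers (3 level I, 26 level II, 28 level III), 4 of them treated. Assumed, because not stated: two-sided 5% tests, AR(1) errors, autocorrelation ρ from 0 to .8.

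**The plan's own figure.** Sample Size says that 10 + 10 points "provides 80% power to detect a change in level of 5 standard deviations (of the predata"). With four coefficients, AR(1) errors and known ρ = .4, the standard error of the level change is 1.001 SD. Power for 5 SD is then Φ(5/1.001 − 1.96) = Φ(3.04), above 99%; 80% power is reached at (1.96 + 0.84) × 1.001 ≈ 2.8 SD. Power was 99–100% at every ρ tried, so the 80% does not reproduce. That is a separate matter, and nothing below depends on it.

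**One 14-point series.** Model: Y_t = β0 + β1·t + β2·D_t + β3·D_t·(t − 11) + e_t, with e_t = ρ·e_(t−1) + u_t, D_t = 1 for t > 10 and β2 = β3 = 0. Residual degrees of freedom: 14 − 4 = 10. Procedure: DW = Σ(r_t − r_(t−1))² / Σr_t² at its exact one-sided 5% point; OLS if not flagged, otherwise AR(1) by Yule-Walker, ML or REML; t on 10 df. There were 20,000 null series per ρ, so the simulation error near 10% is √(0.1 × 0.9/20,000) ≈ 0.2 points. Ranges are over the three estimators.

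| True ρ | DW flags | Level change | Slope change | Either |
|---|---|---|---|---|
| 0 | 5% by construction | 5% | 5% | 8.5% |
| .2 | 11% | 7% | 7% | 13% |
| .4 | 22% | 10% | 10–11% | 18–19% |
| .6 | 33% | 12–13% | 13–16% | 23–26% |
| .8 | 42% | 15–17% | 17–20% | 28–32% |

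At ρ = .4 the mean residual lag-1 estimate is −0.08. Uncorrected OLS rejects 10.3% (level) and 10.9% (slope), so the test-then-correct step changes almost nothing. With 10 post points, the extension the protocol hopes to fund, rejection at ρ = .4 is still about 12% or more per coefficient.

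**One difference series (mean of 4 minus mean of 53).** The inflation is the same when centers do not differ in their change. At ρ = .4, rejection for the level change rises to about 13% and 21% when the between-center SD of that change is 0.5 and 1.0 score SD.

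**All 57 series with one pooled ρ.** The pooled estimate recovers ρ on average (.2, .4, .6, .8), and type I error is about 3.5–6% when centers do not differ in their change. At ρ = .4, a between-center SD of 0.5 or 1.0 in the level change (and a quarter of that per quarter in the slope change) gives 7.7% or 15.9% for level and 5.8% or 7.9% for slope under model-based errors.

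**Center-level inference.** Fit the same model in each center and compare mean changes.
- t-type test: SE = s·√(1/4 + 1/53) = 0.519·s, where s is the between-center SD of the estimated changes. In those two heterogeneous settings type I error is 4.3–5.3%.
- Placebo sets matched on trauma level: 3 × 26 × (28 × 27/2) = 3 × 26 × 378 = 29,484, so a 5% level is attainable. Type I error is 4.4–6.6% for ρ from 0 to .8, stratified or not, with simulation error about 0.6 points.
- Power of the placebo test for a level change at ρ = .4: about 38% for 1 SD and 90% for 2 SD of one center's quarterly score.

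**The case against.** **The protocol does not say that the model is fitted to one series.** This stands in part. Scores exist for all 57 centers, and a fit with a pooled ρ would handle autocorrelation well. Unit of analysis, autoregressive order and estimator are details that an article may leave to an analysis plan. But the testing rule and the series length are fixed here, and under either reading sound inference draws its strength from the other centers.

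**The autocorrelation is borrowed.** This stands. The .4 is not an estimate for this score, and with no autocorrelation the planned procedure holds 5% per coefficient. A reader might infer that false positives are uncontrolled in any event; the documents do not support that.

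**One null trial in five.** The last column of the table invites this reading. It mixes two problems: the either-coefficient rate is already 8.5% at ρ = 0 because two coefficients are tested. The per-coefficient rates are the fair measure of the autocorrelation problem.

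**Seasonality.** Durbin-Watson looks at lag 1 only, and four post quarters are one annual cycle. In an uncontrolled fit, a seasonal swing of amplitude A can produce up to 0.99A of spurious level change and 0.57A per quarter of spurious slope change. The planned concurrent comparison removes any season shared with the controls, so these figures do not describe the plan. Only a season peculiar to the four centers would remain.

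**A placebo test is not the only remedy, nor a complete one.** This stands. A center-level t-type test does as well. The centers are not randomized: all four come from one university network, and the two level III centers are chosen for willingness. A chance shift shared by the four, of SD 0.5 or 1.0, would give about 14% or 29% false positives for level under the placebo test. The planned analysis does not remove such a shift either.

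**Conclusion.** The point holds conditionally. Applied to a single 14-point series or a single difference series, the planned step leaves each nominal 5% test at roughly the uncorrected OLS error rate: no inflation at ρ = 0, a modest excess at .2, about double at .4, and three to four times nominal at .8. This assumes AR(1) errors and two-sided 5% tests. With 57 series and a pooled ρ, the remaining problem is the omission of between-center variation, and its size depends on a between-center SD that the documents do not give.

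A reader might go further and conclude that the 53 controls are ignored, or that placebo sets are required. Neither follows. The controls are already the planned comparator; what is missing is their spread as the basis for the error term, and more than one valid test can use it. The choice should be fixed before post-intervention data are analyzed.

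**What to change.** In Data Analysis, base the primary p-value and interval on center-level changes:

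- For each of the 57 centers, compute the same segmented-regression level change and slope change over the same calendar quarters.
- Compare the four intervention centers with the 53 controls using a test whose error comes from between-center variation. Use either a center-level t-type comparison that accounts for trauma level, or a level-stratified placebo test over the 29,484 sets. Name one as primary.
- Keep the autoregressive segmented regression as the descriptive or secondary analysis.
- State the limits: centers within a level are assumed exchangeable in their change; only two level I controls exist; a shift shared by the four non-randomized centers from one network is not removed.

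The cost is a change of wording and a little programming, since the scores for all 57 centers are already to be collected. P-values will be less favourable and nominal power lower. Part of the apparent power of the single-series test comes from its inflated error rate, so the two should not be compared at face value.
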